### **3.8.2 Data analysis plan**

The results will be summarized for each study group with counts and percentages for categorical variables, mean and standard deviation (SD) or median and interquartile range for quantitative variables, as appropriate. The normality of the quantitative variables will be checked with the Shaphiro-Wilk test.

The c-DEV15plus scale, the performance and time to accomplish specific resuscitation interventions, NASA-TLX, CPT and cardiopulmonary resuscitation metrics will be compared between groups with one-way ANOVA model, followed by the Tukey-Kramer multiple comparisons adjustment procedure in case of statistical significance.

The outcomes will also be analysed with a linear mixed model considering the team as a cluster to evaluate the influence of participants' characteristics on the outcome. To take into account the correlation of the observations within a team, we will specify an undetermined correlation matrix. In case of a not normal distribution of the model residuals, we will proceed with a transformation in order to normalize the distribution.

Both intention-to-treat and per-protocol analyses will be performed.

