**Table 1: c-DEV15plus items for non-shockable PCA simulation scenario**

1. CPR started within 30 seconds (s) from recognition of pulseless state
2. CPR board/rigid surface positioned underneath the manikin within 60 s from recognition of pulseless state
3. Compression/ventilation ratio 15:2
4. Help called (hospital emergency response system activated) within 60 s from recognition of pulseless state
5. Compressors switched more than once during CPR
6. ECG-monitoring started within 60 s from recognition of pulseless state
7. IV/IO access called within 60 s from recognition of pulseless state
8. First epinephrine called within 30 s from recognition of pulseless state
9. First epinephrine administered at the correct dose and dilutiona and by the correct route (IV or IO), followed by a normal saline flush, while compressions are being performed, within 300 s (5 minutes) from recognition of pulseless state
10. Second epinephrine called between 3 and 5 minutes from the first administration of epinephrine
11. Second epinephrine administered at the correct dose and dilutiona and by the correct route, followed by a normal saline flush, while compressions are being performed, within 5 min from the first epinephrine
12. Blood gas called during cardiac arrest
13. Reversible causes treated
14. Shock not administered
15. Medications other than adrenaline (e.g. amiodarone, lidocaine, atropine) not administeredb

---

*Abbreviations:* CPR=cardiopulmonary resuscitation; s= seconds; ECG=electrocardiogram; IV= intravenous; IO=intraosseous; min= minutes. *Note:* a Correct dose of epinephrine is defined as 0.01 mg/kg (or a deviation from the correct weight dose of less than 10%); correct dilution of epinephrine is defined as 1:10.000 (0,1 mg/ml); b Administration of medications to treat identified reversible causes is not considered in this item.

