Each item of the c-DEV15plus is scored either as 0, when the action is performed correctly and timely, as described in the item, or as 1, when the action is not undertaken, undertaken incorrectly, or with wrong timing and, in the event of drug administration, when the dose, duration or route of administration is wrong. The sum of the points attributed to the items represents the c-DEV15plus total score, hence ranging from 0 to 15, with higher scores corresponding to a higher number of deviations from the guidelines. Outcome assessors will score the scenarios through the c-DEV15plus tool using the data registered and coded by the video reviewers.

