### 3.4.2 Secondary outcomes

The following secondary outcome measures will be collected:

- *Performance and time to accomplish critical resuscitation interventions* recommended by PALS guidelines.[6-11,20] The interventions evaluated will be: (i) cardiac arrest recognition (pulselessness); (ii) start of chest compressions; (iii) start of ventilation; (iv) use of a CPR board or a rigid surface underneath the manikin; (v) call for emergency team help; (vi) start of EKG monitor; (vi) first epinephrine administration; (vii) second epinephrine administration; and (viii) treatment of reversible causes of CA. Performance and time to accomplish critical interventions (in seconds) during resuscitation will be assessed and recorded by video reviewers in the study CRFs and will be analysed both as time from the beginning of the scenario and as time from the recognition of pulselessness.
- *Usability of the app*. To assess the PediAppRREST app usability, the team leaders of the intervention group will be administered one validated questionnaire, the System Usability Scale (SUS).[46,47] Further, the team leader will be asked to complete a questionnaire with open-ended questions.
- *Team leaders' workload* measured by the validated, multidimensional NASA-Task Load Index (NASA-TLX).[48,49] This tool includes six subscale scores that represent independent clusters of variables and different domains of the perceived workload: Mental, Physical, and Temporal Demands, Frustration, Effort, and Performance.
- *CPR quality* measured by the Skill Reporter (Laerdal TM), the internal software of the manikin. CPR quality is defined as: i) proportion of chest compressions with depth 50-60 mm; ii) chest compression fraction (the percentage of time during CA with chest compressions), iii) mean chest compression depth; and iv) mean chest compression rate, according to AHA standards.[7,50]

- Team *resuscitation performance* as evaluated with the Clinical Performance Tool (CPT).[40,41] The CPT is a validated scoring system designed based on PALS algorithms, through which sequence, timing, and quality of specific actions, during different simulated scenarios, can be assessed. The CPT section for the asystole will be used to evaluate teams' performance.

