Subsequently, each team participates in a 10-minute standardized intermediate-fidelity simulated scenario of non-shockable PCA caused by hypovolemia and hypoglycemia. A non-shockable rhythm was chosen for the simulated scenario because it is the most common initial cardiac arrest rhythm detected in PCA.[55] The setting, the equipment set up, the scenario, and the manikin (Resusci Junior QCPR Laerdal TM whose head is replaced with the MegaCodeKid Laerdal TM manikin's head, on which advanced air management can be performed) are the same for all the centres. The scenario is introduced by a standardized video where an actress, playing the patient's (manikin's) mother, provides essential clinical information (further scenario details are included in the Appendix 1). The scenarios are conducted off-site, in rooms set up to resemble the Emergency Department Shock room including regularly available equipment. The simulation rooms are set up in a standardized fashion between participating sites. Every team works with one confederate nurse and can call confederate consultants on the phone, who answer based on a standardized script. During the scenario, the team can speak with a facilitator, who is a member of the research team and answers participants' questions following a pre-determined script.

All the scenarios are video-recorded by two different fixed cameras with standardized positions that point to the team and to the monitor. An additional camera captures the actions of the team leaders who use the PediAppRREST app, framing the screen of the tablet. Only the videos from the two fixed cameras will be evaluated by the reviewers. The videos of the team leaders' actions with the tablet will be examined only by the research team to assess potential bugs in the app or challenges with its use.

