### *Simulation scenario*

Case scenario: a case of non-shockable paediatric cardiac arrest caused by hypovolemia and hypoglycaemia.

Team: three paediatric residents and one confederate nurse.

Setting: off-site, in a room set reproducing the environment and the equipment of a paediatric emergency department shock room.

Introduction: A 4-year-old child (22 kg weight) is brought to the Emergency Department by his mother; she refers diarrhoea and vomiting in the past 5 days. Today the boy has been lethargic and difficult to wake up; the triage nurse brings him straight to the shock room.

Information about the clinical case is provided to participants through a video where an actress plays the role of a mother who brings her child to the Paediatric Emergency Department.

The following information about the child are conveyed through the video:

- Age: 4 years;
- Weight: 22 Kg;
- Signs/Symptoms: vomiting and diarrhoea for the previous 5 days, minimal fluid intake for the past 2-3 days;
- Allergies: no allergies;
- Medications: no medications;
- Past history: previously healthy child;
- Last meal: more than 48 hours before;
- Events: child has been sleeping for the previous 2 hours, not responding to physical stimulation.

The scenario starts with a pulseless unconscious child who is suffering a cardiac arrest characterised by pulseless electrical activity (PEA) rhythm for 2 minutes, followed by asystole.

Return of spontaneous circulation (ROSC) is achieved if at least two correct doses of epinephrine are administered timely and hypovolemia +/- hypoglycaemia are addressed. The scenario runs for 10 minutes following the end of the introductory video, regardless of the actions performed by the team.

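### Times to resuscitation interventions are to be compared by one-way ANOVA, although every scenario ends at 10 minutes and a team that never acts has no time

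*Protocol*

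**What the plan says.** Protocol 3.8.2 names the method for several outcomes together: "the performance and time to accomplish specific resuscitation interventions, NASA-TLX, CPT and cardiopulmonary resuscitation metrics will be compared between groups with one-way ANOVA model", with Tukey-Kramer pairwise comparisons if the overall test is significant. It also provides a normality check, a transformation for non-normal residuals of the mixed model, and both intention-to-treat and per-protocol analyses.

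Protocol 3.4.2 defines the outcome: "Performance and time to accomplish critical interventions (in seconds) during resuscitation will be assessed and recorded by video reviewers". It is the first secondary outcome listed, and runs from recognition of arrest to the second epinephrine and treatment of reversible causes. Times are analysed "both as time from the beginning of the scenario and as time from the recognition of pulselessness".

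The observation window is fixed. Protocol 3.6 says "each team participates in a 10-minute standardized intermediate-fidelity simulated scenario of non-shockable PCA", and Appendix 1 says "The scenario runs for 10 minutes following the end of the introductory video, regardless of the actions performed by the team".

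The scoring rule in Protocol 3.4.1 gives a point "when the action is not undertaken, undertaken incorrectly, or with wrong timing", so an action that never happens is a foreseen result. The protocol does not say what time such a team contributes, and it names no method for censored times.

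**The concern.** A team that has not acted by the end of the scenario has no observed time. All that is known is that its time exceeds the window, which is right-censoring. One-way ANOVA needs a number of seconds for every team. If it is run on observed seconds, it compares only teams that acted. Whether a team acts may itself depend on the arm, so this is a subset selected after randomisation, and dropping the rest does not fit the intention-to-treat analysis that 3.8.2 also promises.

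The loss falls where the app might help most. If control teams more often fail to act, their slowest members vanish from the control mean and the arms look more alike than they are. The normality check and the transformation deal with the shape of the distribution; neither supplies a time for an action that did not occur.

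Time to critical interventions is also named among the secondary objectives in Protocol 2.1, so a reader will expect an interpretable result.

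**Working it through.** The protocol gives no time distribution or completion rate, so there is no planned figure to reproduce. Every distribution below is an assumption.

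**Can the window cut off real times?** The checklist limit for giving the first epinephrine is "within 300 s (5 minutes) from recognition of pulseless state". Item 11 allows up to 5 minutes more for the second. Together this is 300 + 300 = 600 s from recognition. The scenario ends 600 s after the introductory video, so once recognition time is added, a team inside both limits can run out of scenario. The window for times from recognition is 600 s minus the team's own recognition time, so no single substitute value fits all teams.

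**Inputs.** Cut-off c = 600 s (3.6, Appendix 1); 35 teams per arm (3.8.1). Assumed: log-normal times, log-SD s = 0.4, median m = 360 s with the app and 540 s in a control arm.

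**Formulas.** With z = ln(c/m)/s:
- completion: P = Φ(z)
- mean part below the cut-off: A = m·exp(s²/2)·Φ(z − s)
- mean among teams that acted: A/P
- restricted mean to 600 s: A + 600(1 − P)

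**App, m = 360.** z = ln(600/360)/0.4 = 1.277; P = 0.899; A = 390.0 × 0.810 = 315.8. Mean among those who acted = 315.8/0.899 = 351 s. Restricted mean = 315.8 + 600 × 0.101 = 376 s.

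**Control, m = 540.** z = 0.263; P = 0.604; A = 585.0 × 0.446 = 260.7. Mean among those who acted = 260.7/0.604 = 432 s. Restricted mean = 260.7 + 600 × 0.396 = 498 s.

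**Differences.** Among teams that acted: 81 s. In restricted means: 122 s. Dropping the others removes about one third of the difference (1 − 81/122 = 0.34).

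**Simulated two-arm power at the 5% level, 35 per arm:**

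| Medians (s) | Drop teams that did not act, t-test | Enter 600 s, t-test | Log-rank, censored at 600 s |
|---|---|---|---|
| 360 / 540 | about 75% | about 98% | about 97% |
| 400 / 600 | about 61% | about 97% | about 97% |

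**When few teams miss the action.** With medians 180 s and 240 s and the same log-SD, completion is 99.9% and 98.9%. The difference is 61 s among teams that acted and 64 s in restricted means, so almost nothing is lost.

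**Reversal in a constructed case.** Let 60% of teams in every arm act at about 300 s, with a further 35% (app) or 5% (control) acting at about 500 s.
- Means among those who acted: app (0.60 × 300 + 0.35 × 500)/0.95 = 374 s; control (0.60 × 300 + 0.05 × 500)/0.65 = 315 s. The app looks slower because more of its teams succeeded. In simulation with two such control arms, ANOVA rejected in 62% of runs.
- Restricted means: app 355 + 0.05 × 600 = 385 s; control 205 + 0.35 × 600 = 415 s. The app is 30 s faster.

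**Dependence on the handling rule.** With the same times among teams that acted (centred on 400 s) and completion of 95%, 60% and 60%, three-arm ANOVA rejected in 5% of runs if the other teams were dropped and in 78% if 600 s was entered.

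**Done or not done.** Under the null with 35 per arm, ANOVA and chi-square rejected at identical rates: 0.049 at a completion rate of 0.5 and 0.037 at 0.95.

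**The case against.** The strongest reply is that the protocol nowhere says that teams which did not act are dropped. How an undone action enters the data could be settled in a statistical analysis plan that is not at hand. For times from scenario start, the window is the same for every team, so entering 600 s makes the arm mean exactly the restricted mean to 600 s. In the illustration that gives 122 s and about 98% power, as good as the log-rank test. All of this stands: the loss of power is conditional on dropping teams. What remains is that the method fixed in 3.8.2 is plain ANOVA with no such rule. Entering one value also does not carry over to times from recognition, where the window differs between teams.

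A reader might infer that every time comparison will be biased. The documents do not support this. The list in 3.4.2 includes recognition and the start of compressions and ventilation, which need not come near 600 s, and no completion rates are given. Nor does the scoring rule in 3.4.1 name actions that are expected to be missed; it is a general rule, and the choice of second epinephrine and reversible causes is a judgement of plausibility.

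A reader might also infer that ANOVA of done/not-done seriously damages the tests. It is the wrong type of model for a proportion, if that is what performance means here, but the check above shows no material effect on the type I error rate.

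**Conclusion.** The point holds for those interventions that some teams do not complete within the scenario. For these, 3.8.2 names a method that does not suit right-censored times and leaves the result to an unstated handling rule. Under the assumed log-normal times with medians 360 s and 540 s, dropping teams cuts the difference from 122 s to 81 s and power from about 97% to about 75%; entering 600 s avoids that loss. Size and direction depend on completion by arm, which the documents do not give. Reversal of sign appears only in a mixture built to show it, and only when teams are dropped.

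The severity is moderate. A reader might infer that the main conclusion of the trial is at risk, but c-DEV15plus counts an undone action as a deviation, so every such team has a score and the primary analysis has no censoring problem.

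**What to change.** In 3.8.2, take the time outcomes out of the ANOVA sentence and state the following:
- Times to interventions are analysed as time-to-event data, censored at scenario end: 600 s for times from scenario start, and 600 s minus the team's recognition time for times from recognition.
- Arms are described by Kaplan-Meier curves and compared by log-rank or Cox, or by restricted mean time to 600 s, with multiplicity-adjusted pairwise contrasts. A restricted mean for times from recognition needs a shorter common horizon, because the window there is below 600 s.
- Done/not-done is compared between arms as proportions, with risk differences.
- ANOVA stays for c-DEV15plus, CPT, NASA-TLX and CPR metrics.

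Stratifying the log-rank test by site and specialty is optional: 4 sites × 3 specialties gives up to 12 strata for 70 teams in each pairwise comparison.

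The cost is a change of wording and slightly more analysis work. No new data are needed, because the video reviewers already record both the actions and their times.

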## 1. ABSTRACT

**Introduction:** Paediatric cardiac arrest (PCA), despite its low incidence, has a high mortality. Its management is complex and deviations from guideline recommendations occur frequently. We developed a new interactive tablet app, named PediAppRREST, to support the management of PCA. The app received a good usability evaluation in a previous pilot trial. The aim of the study is to evaluate the effectiveness of the PediAppRREST app in reducing deviations from guideline recommendations in PCA management.

**Methods and analysis:** This is a multicentre, simulation-based, randomized controlled, three-parallel-arm study. Participants are residents in Paediatric, Emergency Medicine, and Anaesthesiology programs in Italy. All 105 teams (315 participants) manage the same scenario of in-hospital PCA. Teams are randomized by the study statistician into one of three study arms for the management of the PCA scenario: 1) an intervention group using the PediAppRREST app; or 2) a control group (CtrlPALS+) using the Paediatric Advanced Life Support (PALS) pocket reference card; or 3) a control group (CtrlPALS-) not allowed to use any PALS-related cognitive aid. The primary outcome of the study is the number of deviations (delays and errors) in PCA management from PALS guideline recommendations, according to a novel checklist, named c-DEV15plus. The c-DEV15plus scores will be compared between groups with a one-way ANOVA model, followed by the Tukey-Kramer multiple comparisons adjustment procedure in case of statistical significance.

**Ethics and dissemination:** The Ethics Committee of the University Hospital of Padova, coordinating centre of the trial, deemed the project to be a negligible risk study and approved it through an expedited review process. The results of the study will be disseminated in peer-reviewed journals, and at national and international scientific conferences. Based on the study results, the PediAppRREST app will be further refined and will be available for download by institutions/health care professionals.

**Trial registration number:** NCT04619498

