### **3.2 Participants**

Participants are recruited from medical residency programs in Paediatrics, Emergency Medicine and Anaesthesiology, at the i) University Hospital of Padua, University of Padua (Padua); ii) Meyer University Hospital, University of Florence (Florence); iii) Maggiore della Carità University Hospital, University of Piemonte Orientale (Novara); and iv) Agostino Gemelli University Hospital, Catholic University of Sacred Heart (Rome).

[figure not shown]

Figure 1. Study design diagram

Eligibility of potential participants is assessed by the study investigators of each participating site. Residents must meet all the following criteria to be enrolled in this trial: i) to be attending a residency training program in Paediatrics, Anaesthesiology or Emergency Medicine; ii) to be BLS (Basic Life Support) or P-BLS (Paediatric-Basic Life Support) or PALS or ALS (Advanced Life Support) or ACLS (Advanced Cardiac Life Support) certified, following the AHA or the European Resuscitation Council (ERC) recommendations; and iii) to give consent to participate to the study and to be video-recorded. Additionally, to be eligible for the role of team leader residents must be PALS-certified according to AHA or ERC guidelines. Residents who took part in the pilot study of the PediAppRREST app,[37] or who are unable to attend the simulation sessions because of maternity/paternity leave, sick/personal leave or training abroad are not eligible to participate in the trial.

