### **3.3 Randomization, allocation concealment, and blinding**

Participants are randomized by the study statistician in teams of three, stratified by study site and residency program specialty. Randomization is conducted assuring that in every team there will be at least one PALS-certified team member assigned to the role of team leader. The same statistician assigns a unique team identification number to each team and prepares the list of participants associated with each team to be sent to the principal investigators. Participants are randomly divided in teams of three members per each scenario; the team leader is selected among PALS-certified residents whereas the other two members have to be at least BLS-certified. The teams are randomized with a 1:1:1 ratio in the intervention arm (PediAppRREST arm) and the two control arms.

The statistician also creates opaque sealed envelopes externally marked with the team identification number and containing a paper slip, which indicates the arm allocation for that specific team. Team group allocation is concealed until the simulation sessions. Randomization of participants to teams, and teams to the arms, is performed with SAS 9.4 (SAS Institute Inc., Cary, NC, USA) for Windows.

Due to the nature of the cognitive support tools used in the trial, blinding of participants as well as of research staff involved in the simulation sessions and video reviewers, is not possible. However, blinding of the statistician performing data analysis will be ensured. Data analysis is expected to be finalized by February 2022.

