## **3.6 Study procedures**

Participant recruitment and assessment will take place over a 15-month period (September 2020 – December 2021). The University Hospital of Padua is the coordinating centre of the trial. Its research team will oversee all study procedures and processes during the simulation sessions to assure standardised high-quality procedures are carried out at each participating centre (Padua, Florence, Novara, Rome). At the trial simulation sessions, the research staff meet the residents, illustrate the study, answer any possible questions, re-assess eligibility criteria for each participant, and obtain informed consent for study participation and video recording.

During all trial sessions measures to prevent COVID-19 infection spread (physical distancing, hand hygiene, use of personal protective equipment during the scenario, temperature and health checks, contact tracing, surfaces/mannequin/equipment disinfection, etc.) are strictly followed for participants and research staff's safety.[53,54]

Before beginning the simulation session, all teams watch the same 20-minute briefing video about the study procedures and orientation to the setting, manikin, and equipment. This phase has also the aim of increasing participants' adherence to intervention protocols and study procedures.

After the briefing, each team progressively receives and opens its assigned sealed envelope, which contains the arm allocation (PediAppRREST or CtrlPALS+ or CtrlPALS-). Thereafter, all participants wear a sticker with the corresponding team identification number and personal identification code. Ten minutes before their assigned simulated scenario each team is informed that the scenario will be about a PCA case, without specifying any further detail. The teams assigned to the intervention arm (PediAppRREST) watch a 5-minute tutorial video about the app and its use, prepared ad-hoc for this study. They are also given five minutes to practically

familiarize with the tablet and the app. The teams in the CtrlPALS+ arm are given five minutes before the scenario to familiarize with the PALS pocket algorithm card, while teams in the CtrlPALS- arm are given five minutes to discuss how to manage the scenario without any PALS-related cognitive aid.

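### The primary one-way ANOVA leaves out site and specialty, the two factors used to stratify the randomisation; adding them would gain precision at almost no cost

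*Protocol*

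**What the plan says.** **Design.** Protocol section 3.3: "Participants are randomized by the study statistician in teams of three, stratified by study site and residency program specialty". Allocation to arms comes later in the same paragraph: "The teams are randomized with a 1:1:1 ratio in the intervention arm (PediAppRREST arm) and the two control arms". That sentence does not mention stratification. Section 3.2 names four university hospitals and three specialties: "Participants are recruited from medical residency programs in Paediatrics, Emergency Medicine and Anaesthesiology". There are therefore up to 4 × 3 = 12 strata.

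**Analysis.** Section 3.8.2 says c-DEV15plus and most secondary scores "will be compared between groups with one-way ANOVA model, followed by the Tukey-Kramer multiple comparisons adjustment procedure" if the overall test is significant. The abstract repeats this for the primary outcome: "The c-DEV15plus scores will be compared between groups with a one-way ANOVA model". Section 3.8.1 sizes the trial on the same single-factor model. None of the three places includes site or specialty.

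**Additional model.** Section 3.8.2 continues: "The outcomes will also be analysed with a linear mixed model considering the team as a cluster to evaluate the influence of participants' characteristics". This model comes on top of the ANOVA and serves another purpose. It does not name site.

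**The concern.** Site and specialty were judged important enough to stratify on, yet the primary model ignores both. When arms are balanced within strata, differences between strata cancel out of the arm contrast. A model with arm alone still counts them as residual variance, so the standard error is overstated, the test rejects less often than its nominal 5%, and the intervals are wider than they need be.

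When arms are not balanced within strata, a different cost arises: an arm that happens to receive more teams from a stronger specialty or site keeps that advantage in its estimate.

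What is at stake is precision. It matters most for the app against the pocket card, where both arms have an aid and a difference below 3.00 points is plausible. The one-way model is fixed in the protocol itself, so this is not a detail left to a later analysis plan.

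**Working it through.** **Inputs from the protocol (3.8.1):** SD 2.20; target difference 3.00 points; Tukey-Kramer at 5%; 29 teams per arm raised by 20%, that is 29 × 1.2 = 34.8, so 35 per arm and 105 in all.

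**Assumed:** R², the share of score variance explained by site and specialty, at 0, 10, 20 and 30%. The protocol gives no figure.

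**The plan's own figure.** Per-pair Tukey power for 3.00 points at SD 2.20 reaches 80% at 12 per arm (80.7%) and is 99.7% at 29, so the stated 29 does not reproduce. That is a separate matter; what follows uses the planned 35 per arm.

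**Degrees of freedom.** One-way model: 105 − 3 = 102. Main effects for site and specialty cost (4 − 1) + (3 − 1) = 5, leaving 97. The 5% studentized range points for three groups are q = 3.364 (102 df) and 3.366 (97 df).

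**Reading A: arms balanced within strata.**

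- Unadjusted half-width: q × SD/√n = 3.364 × 2.20/√35 = 1.25 points, whatever R² is.
- Adjusted half-width: 3.366 × 2.20 × √(1 − R²)/√35.
- True familywise error of the unadjusted procedure: P(studentized range > 3.364/√(1 − R²)). The cut-offs are 3.364, 3.546, 3.761 and 4.020.
- Power at 1.5 points: noncentral t with true standard error 2.20 × √(1 − R²) × √(2/35) = 0.526, 0.499, 0.470, 0.440. The adjusted critical value is 3.366/√2 = 2.380; the unadjusted one is effectively (3.364/√2)/√(1 − R²) = 2.378/√(1 − R²).

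| R² (assumed) | True familywise error, unadjusted | Half-width unadjusted / adjusted | Power at 1.5 points unadjusted / adjusted |
|---|---|---|---|
| 0% | 5.0% | 1.25 / 1.25 | 68% / 68% |
| 10% | 3.6% | 1.25 / 1.19 | 69% / 73% |
| 20% | 2.4% | 1.25 / 1.12 | 70% / 79% |
| 30% | 1.5% | 1.25 / 1.05 | 71% / 85% |

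Unadjusted power also rises with R², because balance reduces the true variance of the contrast. The gain from adjustment is therefore about 4, 9 and 13 percentage points at 10, 20 and 30% (before rounding).

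A simulation (5,000 trials per setting, 12 equal strata, blocks of three) agrees. The one-way F test rejects in 4.7/3.9/2.5/1.4% of null trials, against 4.6/5.4/4.9/4.5% with strata in the model.

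**At the planned effect.** For 3.00 points at 35 per arm, power is at least 99.9% with or without adjustment.

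**Reading B: only team formation stratified.** The simulated type I error of the one-way test is 5.2 to 5.4%, so it is not conservative. Chance imbalance adds random error to an arm difference with SD 2.20 × √R² × √(2/35) = 0.17/0.24/0.29 points at 10/20/30%. With all 12 strata as separate terms, the full Tukey width was 2.64/2.51/2.37/2.21 at 0/10/20/30%, against about 2.50 unadjusted. This is a loss at 0%, about even at 10% and a gain at 20 to 30%. That model spends 11 df; the main-effects model proposed here spends 5.

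**The case against.** A reader might infer that the planned test is conservative and its intervals too wide as a matter of fact. The protocol does not support that. In section 3.3 stratification is attached to forming participants into teams, and the 1:1:1 sentence does not repeat it. Under the narrower reading the test holds its level. The conservative test and the uncorrected imbalance belong largely to opposite readings, so they should not be added together. This objection stands, and the point is conditional because of it.

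The size is assumed throughout. Team leaders must be PALS-certified, and the scenario, manikin, briefing and rooms are standardised across centres, so stratum differences may be small. At 0% nothing is gained. This stands too.

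The 1.5-point difference is illustrative and not the plan's target. Power at 2.0 points is already 92% unadjusted. The one-way model also matches the one used for sizing, so the plan is consistent with itself. Both remarks are correct, and they limit the point to precision.

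The weakest defence is the mixed model. Type of residency is collected (section 3.6) and could enter it, but the covariates are not listed, site is not named, and the model supplements the primary comparison without replacing it.

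**Conclusion.** The point holds as a precision improvement. The protocol stratifies by site and specialty and then fixes a primary model without them. If arm allocation was balanced within strata that explain 10 to 30% of the variance, true familywise error falls to between 3.6% and 1.5%, intervals are 5 to 16% wider than the data require in terms of the unadjusted width (1.25 against 1.19 to 1.05), and about 4 to 13 points of power are lost at 1.5 points. If only team formation was stratified, the level is correct, and what is lost is the correction of chance imbalance, plus precision when the strata are clearly prognostic.

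It would be wrong to conclude that the primary result would be invalid. Under one reading the error is on the safe side, under the other the level is kept, and power at 3.00 points is at least 99.9% with either model. All sizes rest on the assumed stratum variance, the stated SD of 2.20 and the full 35 teams per arm.

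**What to change.** - In section 3.8.2 and the abstract, make the primary model a linear model of c-DEV15plus on arm, site and specialty (main effects only), with Tukey-Kramer contrasts of the adjusted arm means.
- Keep the one-way ANOVA as a supporting analysis.
- Use the same terms for CPT, NASA-TLX and the CPR metrics.
- In section 3.3, state whether allocation of teams to arms was itself stratified by site and specialty.

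The cost is a sentence or two and 5 of 102 error degrees of freedom. No new data are needed, since both factors are known from randomisation. The change should be made before the data are analysed, so that the covariates are pre-specified.
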